## Methods: participants, interventions, and outcomes

### Study setting {9}

General practices in Queensland and Victoria, Australia.

### Eligibility criteria {10}

#### Inclusion and exclusion criteria for general practices

Practices will be included if they are in Queensland or Victoria, use electronic health record (EHR) software compatible with the National Cancer Screening Register (NCSR) (Best Practice, Medical Director Version 4) and are willing to download the free NCSR application which provides a portal between the NCSR and the general practice EHR. Practices will be eligible if they have at least two full-time equivalent (FTE) GPs working in their general practice and have a practice manager (or delegate) who will champion the study throughout the trial period. General practices geographically located in very remote areas, as defined by the Modified Monash Model (MMM) category 7 [17], which includes offshore and central Australian locations, will be excluded for logistical reasons [17].

Practices will not be approached where it is known that they have been involved in recent research projects in cancer screening or are involved in other bowel cancer research projects at the University of Melbourne, or cancer screening quality improvement programmes for example those conducted by the local Primary Health Networks.

Under the NBCSP ‘hot zone policy’, the NBCSP suspends sending out kits for up to 6 months of the year to certain areas defined by postcode due to extreme heat during summer (correspondence from the NBCSP). Practices will be ineligible if they are in areas classified as ‘hot zones’ as their patients will not receive a kit during some or all the trial intervention period. ‘Hot zones’ account for 111 (25%) of 447 postcodes and 367 (23%) of practices in Queensland (none in Victoria), and therefore practices sampled will still represent most practices in Queensland [5]. General practices in Australia can operate as independent small businesses or as larger businesses with multiple different clinics. When practices in different physical locations have combined EHRs for patients at all practices, these practices will be treated as one practice in the trial. The “main practice” will be defined as the practice location that the owner or staff identify as being the principal practice. If the practice is in the treatment group, the phone number (and logo) of the main practice will be the one sent in the SMS to all patients.

When more than one practice shares EHRs but identify as separate practices (i.e. they do not share the same logo and/or name), and whose patient records cannot be separated, they will not be included in the trial. In the unusual case where more than one practice shares EHRs, but if one is in a hot zone and one is not, only the patients living outside of the hot zone will be included in the study. This will be defined by patient residence postcode in the EHR.

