## Introduction

### Background and rationale {6a}

Australia has one of the highest rates of colorectal cancer (CRC) in the world [1]. Currently, 40% of CRC cases are diagnosed at stage 3 or 4 leading to a poorer prognosis [2]. Screening for precancerous adenomas and early-stage cancer, at which time they can be easily treated, improves outcomes and is cost-effective [3, 4]. Australia has a National Bowel Cancer Screening Program (NBCSP), which is a coordinated, population-based screening programme that sends immunochemical Faecal Occult Blood Test (FIT) kits to eligible Australians aged 50 to 74 years every 2 years. The kits are free and sent directly to a person’s home where two samples can be self-collected and returned for testing [5]. Despite the convenience of this process, uptake of the NBCSP is only 40.9% with fewer people in the younger age groups completing the kit; currently, only 31.6% of people between 50 and 54 years return the kit for testing [6]. Modelling has estimated that if screening participation increased by an additional 10%, 24,300 additional CRC diagnoses and 16,800 additional CRC deaths could be prevented, and an additional $300 million dollars in healthcare expenditure saved over the next 25 years in the Australian population [7].

Multiple strategies have been tested to increase CRC screening uptake, all having varying degrees of success either as single or multifaceted interventions [8]. Of these, endorsement from a patient’s general practitioner (GP) has been demonstrated to have one of the biggest impacts on increasing uptake [9, 10]. Direct engagement by GPs with their patients increases patient awareness about screening and reduces anxiety and fear about participating in screening [11]. In Australia, the kit is sent directly to the participant from the NBCSP, and currently, there is no coordinated and efficient way for the GP to prompt or encourage their patients to participate in screening.

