The intervention period will be for 6 months (26 weeks). The staff (funded by the research team) in the NCSR will then generate datasets for each week of the intervention period that include all patients who are due a SMS that week based on ‘Date SMS is due’ (Dataset 4). This date will be calculated so that the SMS will be sent on a Sunday for kits due 3 days on either side of that date. Each dataset will only include the Unique Record ID, Patient’s first name, and mobile number. The name of the file will identify the GP practice and the date when the SMS are due to be sent. All 26 NCSR datasets created for each general practice will be saved as separate encrypted.csv files and sent using a secure file transfer portal to the general practice.

The general practices in the intervention arms will be instructed to transfer the NCSR.csv datasets that have been separated into 26 weekly files. These will then be uploaded to the GoShare platform and scheduled for sending the SMS/SMS plus bundle on the Sunday they are due (approximately 2 weeks prior to the kit being sent). The control arm practices will not be provided access to the NCSR datasets until the end of the trial.

##### Step 6

At the end of the intervention period:

Using the Dataset 3 created in Step 5, the NCSR will add an additional variable ‘Date the kit was returned’ for each person. If there is no date for a returned kit, then a reason as to why the person was not sent the kit will be added in a separate field—this will happen if there has been a concurrent event (e.g. patient had a colonoscopy, opted out or deferred their screening, was diagnosed with colorectal cancer, or had a FIT test from elsewhere recorded), or the field will be left blank with the assumption that the person did not return the kit within 6 months of the due date of the NBCSP kit. The NCSR dataset (Dataset 5) with the added kit return dates will be stored on the NCSR secure server as a.csv dataset and downloaded by secure file transfer by the practice when needed.

##### Step 7

Dataset 6 will be created using Dataset 5, where individual identifying information (such as name, address, and mobile number) will be removed, and provided to the research team for analysis. The dataset may be securely transferred to the research team via the GP Practice (once the records have been de-identified) or directly from NCSR.

##### Step 8

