## Trial status

The SMARTERscreen trial has approval from the Human Research Ethics Committee at the University of Melbourne and started recruitment on 12 February 2023. Protocol is dated 7 June 2023; version 1.0.

All practices have been recruited (21 July 2023) and we anticipate data extraction from the NCSR will begin in September 2023. The intervention period will begin once recruitment and baseline data have been collected. The intervention will begin in early 2024 once individuals’ eligibility is determined and randomisation is implemented.

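### The hot-zone exclusion follows the practice's address although kits are mailed to homes, so some Queensland patients whose kit is suspended may enter the trial and be recorded as non-returners

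*Protocol article*

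**What the plan says.** The practice eligibility criteria explain that "the NBCSP suspends sending out kits for up to 6 months of the year to certain areas defined by postcode", because of summer heat. Practices in such areas are excluded, "as their patients will not receive a kit during some or all the trial intervention period". Hot zones are put at 111 of 447 Queensland postcodes (25%) and 367 Queensland practices (23%), with none in Victoria. The Background section says of the kits: "The kits are free and sent directly to a person’s home".

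The patient's own address is used in one situation only. Where practices share records and one is inside a hot zone and one outside, only patients living outside it are included: "This will be defined by patient residence postcode in the EHR". The patient eligibility criteria contain no hot-zone item. They require a kit due within the trial period according to the register.

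On counting, Criteria for discontinuing {11b} and Outcomes {12} both remove patients not sent a kit, and Outcomes defines a non-returner as someone who was sent one. In Step 6 of The method (Fig. 4), the register adds the return date. If there is none, it adds a reason the kit was not sent where a concurrent event is on record, "or the field will be left blank with the assumption that the person did not return the kit within 6 months of the due date". On timing, Trial status says: "The intervention will begin in early 2024 once individuals’ eligibility is determined and randomisation is implemented".

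**The concern.** Suspension acts on the address the kit is mailed to, but the exclusion acts on the address of the practice. A hot-zone resident who attends a practice outside the zone passes every written eligibility check if the register shows a kit due. In the two SMS arms that person is told a kit is on its way while dispatch may be suspended. In the control arm there is no message, but the kit may be missing all the same.

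At stake is the primary denominator. Patients who could not return a kit in time, if kept as non-returners, pull all three arms' proportions towards zero and shrink every absolute difference. This could happen only in Queensland, so it also touches the analysis of effect by practice location, a stated secondary aim.

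**Working it through.** **Can these patients be removed by the data as described?** The outcome definition needs to know whether a kit was sent. Three features of the data flow bear on this.

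- The reasons listed in {11b}, {12} and Step 6 are opting out, temporary hold or deferral, bowel cancer diagnosis, recent colonoscopy and a FIT elsewhere. Suspension is in none of the lists.
- The fields described in Steps 4 and 6 include the due date and the return date, but no date sent.
- Step 7 removes the address before the analysis file is supplied, so the problem may not be recoverable later.

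This leaves two routes to a non-return code.

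1. No kit was sent in the period, no reason was recorded, and the blank is read as non-return. This contradicts {11b} and {12}.
2. A kit was sent late but within the 26-week intervention period. The outcome window runs 6 months from the due date, so a delay of d weeks leaves about 26 − d weeks to return it. This patient was sent a kit, so the exclusion does not apply.

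**The plan's own sample size.** Inputs from Sample size {14}: two-sided alpha 0.017 per comparison, ICC 0.01, mean 260 patients per practice, coefficient of variation 0.76, and 34% vs 44% and 44% vs 51.5%. There are 21 practices per arm, one of them spare.

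- Design effect = 1 + ((0.76² + 1) × 260 − 1) × 0.01 = 5.092.
- Effective patients per arm with 20 practices = 20 × 260 / 5.092 = 1,021.
- For 44% vs 51.5%, 924 patients per arm are needed before clustering: 924 × 5.092 / 260 = 18.1 practices.
- Normal-approximation power with 20 practices per arm: 98.8% for 34% vs 44%, and 84.4% for 44% vs 51.5%.

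The claim that 63 practices suffice is reproduced.

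**Dilution.** Let f be the share of due patients in included Queensland practices who get no kit in time and are coded as non-returners. The protocol gives no value, so f is an assumption. Half the practices are in Queensland (Trial design {8}). With equal practice sizes, differences are multiplied by (1 − f) in Queensland and by (1 − f/2) overall.

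| f (assumed) | 10-point difference, Queensland | 10-point difference, overall | 7.5-point difference, overall | Power vs control | Power, bundle vs SMS only |
|---|---|---|---|---|---|
| 0 | 10.0 | 10.0 | 7.50 | 98.8% | 84.4% |
| 2% | 9.8 | 9.9 | 7.43 | 98.7% | 83.6% |
| 5% | 9.5 | 9.75 | 7.31 | 98.5% | 82.3% |
| 10% | 9.0 | 9.5 | 7.12 | 98.1% | 80.2% |
| 15% | 8.5 | 9.25 | 6.94 | 97.6% | 78.0% |
| 25% | 7.5 | 8.75 | 6.56 | 96.3% | 73.3% |

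If the same patients are excluded instead, the differences stay at 10 and 7.5 points, and power at f = 10% is 98.7% and 83.9%. All rows hold the ICC at 0.01.

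**The case against.** The strongest reply is that the written definition already deals with this: a patient not sent a kit is ineligible, and a non-returner must have been sent one. The reasons in {11b} and Step 6 are given as examples, so the register could enter suspension as a reason. This stands against the stronger reading that a reader might infer, namely that hot-zone residents are counted as non-returners. The documents do not support that as a fact. They support only that the described dataset may fail to separate these patients, and that Step 6 and the outcome definition disagree on what a blank means. That disagreement affects any unrecorded non-dispatch, not only hot zones.

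Second, register due dates may already reflect suspension. The patients would then not be due in the period, or would get the SMS at the right time. This is possible and would largely remove the problem. However, the protocol does not say so, and its own practice-level and shared-record exclusions suggest that the due date alone was not relied on.

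Third, the size is assumed and the formula is an upper bound for a given share of hot-zone residents. Suspension lasts up to 6 months, the 26 weeks may run past it, and a delayed kit can still come back in time. This stands. The 25% and 23% figures describe postcodes and excluded practices, so they do not measure the affected share in included practices.

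Fourth, suspension depends on residence and season, not on arm. This also stands: the documents give no ground for reading it as bias towards any arm.

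**Conclusion.** The mismatch between the practice's address and the mailing address is real, and the data flow as described does not reliably catch its consequences. Some hot-zone residents of included Queensland practices may be recorded as non-returners, provided that register due dates do not already allow for suspension.

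The effect is modest. With an assumed 2–10% of Queensland patients affected, a 10-point difference becomes 9.9–9.5 points overall and 9.8–9.0 in Queensland. The comparison with least margin, bundle versus SMS only, drops from about 84% to 80% power at 10% and falls below the 80% target at 15%. Comparisons with control keep more than 96% power even at 25%.

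A reader might also infer a false finding in the location subgroup. Within the 2–10% range the Queensland difference moves by at most 1 point, and nothing here shows that an interaction test would detect it. The case for acting is that the repair is cheap and is best made before allocation.

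**What to change.** - Before randomisation, apply the residence-postcode rule now reserved for shared-record practices to every Queensland practice, at least for patients whose due date falls within the suspension period. A date-limited filter needs the register's due date, so it belongs after Step 4. Randomisation already follows the return of the enriched lists.
- Add hot-zone suspension of dispatch to the reasons for the not-sent code in {11b}, {12} and Step 6.
- Add the date the kit was sent to the Step 6 dataset. This identifies both unsent and late kits directly.
- Reconcile the blank-field rule in Step 6 with {11b} and {12}, so that non-return is assigned only where a kit is known to have been sent.
- State whether register due dates take suspension into account.

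The cost is one postcode filter, one reason code and one extra register field. The eligible list becomes slightly smaller in practices near a hot-zone boundary. A filter not limited by date would also drop some patients whose kits would have been sent validly after suspension ended.

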#### Inclusion and exclusion criteria for patients

Eligibility:1) Assessed at the general practice.People will be eligible if:They are aged between 49 and 60 years old during the trial period.They are a regular patient at a general practice recruited into the trial (defined by their patient file having been opened at least three times in the previous 2 years).They have a mobile phone number recorded in the practice.They have a Medicare number recorded in the practice.They have not opted out of receiving SMS from their practice.They do not have a diagnosis of CRC in their EHR.2) Assessed at the NCSR.People identified as eligible in the general practice records will be linked with NCSR records and remain eligible for the trial if:They have matching record in the NCSR database.They are due to receive their NBCSP kit within the trial period.People will be excluded if:Their record extracted from the general practice EHR does not match with the records in the NCSR database.They have a diagnosis of CRC recorded in their NCSR record.They have opted out from receiving the NBCSP kit, as recorded in their NCSR record.They have put their NBCSP kit on hold, as recorded in their NCSR record.They have died, as recorded in their NCSR record.They are not due for screening because they have had a recent colonoscopy, as recorded in their NCSR record.They are not due for screening because they have had a recent FIT elsewhere, as recorded in their NCSR record.

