#### Recruitment {15}

General practices will be identified for recruitment in the following ways: through the Department of General Practice and Primary Care at the University of Melbourne primary care practice-based research and education network, which includes general practices in Victoria and a smaller number in Queensland who are engaged with any research and/or teaching with the University of Melbourne; through the Queensland Cancer Council database of general practices who have expressed an interest in being involved in research; through the research team’s professional networks; snowballing based on advice from other practices; and cold-calling practices identified through web-based searches.

The recruitment will involve initially contacting the general practices by telephone to introduce the project and to organise a face-to-face meeting to explain the trial in more detail. If eligible (see above) and interested, the project officers will arrange to meet with the general practice staff—either face-to-face or on Zoom—to double-check the practice meets the eligibility criteria and explain the trial requirements including details about the intervention. The project officers will ensure all staff know about the trial before it starts and set up a process for staff to contact them if they have questions or to let them know if there are any staff changes during the trial. Two senior practice staff will then provide consent on behalf of the general practice.

Patients will not be individually recruited as the research team will only have access to de-identified data from the general practice that has been collected from the NCSR.

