#### The method (Fig. 4)

##### Step 1

The eligible patient list will be collected from each general practice EHR using a bespoke Structured Query Language (SQL) query. The list will be saved as a comma-separated values (.csv) file securely on the practice computer, with a name specific to the study identifier of the practice (practice ID) and the date of extraction (Dataset 1).

##### Step 2

The practice manager will add three columns of data including (1) a column with a Provider number for the principal GP for that practice, (2) a column with a unique trial ID code for each patient (e.g. GP0010001), and (3) a column with a unique practice ID code for each practice (e.g. GP001) (Dataset 2).

##### Step 3

This dataset will be saved as a.csv file and uploaded to the NCSR using a secure file transfer protocol (SFTP).

##### Step 4

Once the NCSR have the.csv file (Dataset 2), they will match the patients in the NCSR by date of birth, Medicare number, and name. The.csv file will be enriched with five additional columns of data for each person: one for the date they returned their last NBCSP kit (or blank if they have not returned one before) [‘Date_kit_returned’], one with the date their next NBCSP kit is due [‘Date_Kit_Due’], one if the NCSR cannot match patients’ identifying data with the register’s records [‘1’ if records match with NCSR database, ‘0’ if data in the.csv file does not match the register], one calculating the date the SMS will be sent [‘Date SMS is due’ which will be calculated as the (‘Date the NBCSP kit is due’ − 14 days)], and one calculating the patient’s age at the time when their kit is due [‘Age in months when kit is due’, which will be calculated as (= ‘Date the NBCSP kit is due’ − ‘Date of Birth’ in years, multiplied by 12)].

The NCSR will then save a.csv file (i.e. NCSR dataset) for every practice (Dataset 3).

##### Step 5

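### A person can qualify at more than one trial practice and the described data flow never compares practice lists, so some people may be recorded twice, often in two arms; the likely bias is small

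*Protocol article*

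**What the plan says.** Under Inclusion and exclusion criteria for patients, eligibility is assessed first at the practice. A person must be a regular patient of a recruited practice, "defined by their patient file having been opened at least three times in the previous 2 years". The register-stage exclusions that follow cover failed matching, cancer diagnosis, opting out, kits on hold, death, recent colonoscopy and a recent FIT elsewhere. None covers a person already listed by another trial practice.

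The practice-level criteria recognise that practices may belong to "larger businesses with multiple different clinics", but the rules there deal only with sites whose electronic records are combined or shared. They do not address one person with separate files at two practices.

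The method (Fig. 4) sets out the data flow:

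- Step 2: each practice manager adds "a column with a unique trial ID code for each patient (e.g. GP0010001"), an example that carries the practice code.
- Step 4: on receiving a practice's list, the NCSR staff act as follows: "they will match the patients in the NCSR by date of birth, Medicare number, and name". The output is again per practice: "The NCSR will then save a.csv file (i.e. NCSR dataset) for every practice (Dataset 3").
- Step 5: 26 weekly SMS files are made for each practice.
- Step 7: the analysis file is created, in which "individual identifying information (such as name, address, and mobile number) will be removed".

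Recruitment {15} lists several routes, including "snowballing based on advice from other practices". Sequence generation {16a} places randomisation after the enriched lists have gone back to the practices.

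**The concern.** Three file openings in 2 years does not tie a person to a single practice, and Step 4 matches patients to the register, not practice lists to each other. A person on two lists therefore receives two trial IDs and contributes the same kit and the same outcome twice.

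Three things follow:

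- If one listing is in a control practice and the other in an SMS practice, the control record belongs to someone who was texted.
- If one is in the SMS only arm and the other in the SMS bundle arm, the person gets both messages, and the contrast between those arms is diluted.
- The planned generalised estimating equations allow for clustering within practices but take practices as independent, which shared patients violate.

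This goes beyond missing detail, because the stated eligibility rule and the stated sequence of steps themselves create the double entry.

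**Working it through.** **Inputs from the document.** 63 practices allocated 21:21:21; on average 260 patients per practice, coefficient of variation (CV) 0.76; intraclass correlation 0.01; alpha 0.017 per comparison; planned rates 34% (control), 44% (SMS only) and 51.5% (bundle); one spare practice per arm.

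**The plan's own figure.** Design effect = 1 + ((0.76² + 1) × 260 − 1) × 0.01 = 5.092. Effective size with 20 practices per arm = 20 × 260 / 5.092 = 1,021. For the hardest contrast (44% vs 51.5%), using a t reference with 2(k − 1) degrees of freedom, power is 78.9% with k = 19 per arm and 81.5% with k = 20. So 20 is the smallest number reaching 80%; adding one gives 21 per arm and 63 in all. The sample size reproduces.

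**Chance of two arms, given overlap.** Once one practice is placed, 42 of the other 62 are in a different arm: 42/62 = 67.7%. Within one stratum of 12 to 21 practices (assumed sizes) it is about 70% to 73%. The remaining 20/62 = 32% (unstratified) fall in the same arm.

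**Dilution.** The overlap rate is not given. Let f be the share of the 63 × 260 = 16,380 records that belong to people also listed at a second trial practice. Assume that such a person responds at the higher planned rate of the arms they are in. Then:

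- Control rate = 34 + f × (21/62) × (10 + 17.5)
- SMS only rate = 44 + f × (21/62) × 7.5
- SMS only minus control = 10 × (1 − f × 42/62)
- Bundle minus SMS only = 7.5 × (1 − f × 21/62)

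| Assumed f | People listed twice (f × 16,380 / 2) | Control records exposed to an SMS | SMS only − control | Bundle − SMS only |
|---|---|---|---|---|
| 1% | 82 | 0.7% | 9.93 | 7.47 |
| 5% | 410 | 3.4% | 9.66 | 7.37 |
| 10% | 819 | 6.8% | 9.32 | 7.25 |

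**Power.** Putting the diluted rates into the same t-based calculation, power for bundle vs SMS only goes from 81.5% to 81.2%, 79.9% and 78.3% at 20 practices per arm. At the planned 21 it goes from 83.7% to 83.5%, 82.3% and 80.7%.

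**How plausible is each f?** The article says that 367 practices are 23% of Queensland's. That implies 367/0.23 ≈ 1,596 in total and about 1,229 outside hot zones. Half of 63 is about 32, or 2.6% of those. If 20% of patients (an assumption) were regular at a second practice, and that practice were a random one outside the hot zones, f would be about 0.2 × 2.6% ≈ 0.5%, and the 10-point contrast would become 9.97. Even if every patient had a second practice, random placement gives only about 2.6%. Local clustering of trial practices would raise this. No Victorian count is given.

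**What the analysis file could show.** It derives from a file holding kit due date, previous and new return dates, and age in months when the kit is due. Among 16,380 × 16,379 / 2 ≈ 134 million pairs, and assuming uniform and independent values, chance matches on due date (182 days), age in whole months (144) and sex (2) number 134,144,010 / 52,416 ≈ 2,560. If age were exact to the day (4,383 days in 12 years), about 84 would remain. At f = 1% there would be 82 true pairs among these. Return dates help only for people who have returned a kit.

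**The case against.** The strongest reply is that this is a condensed article. Removing duplicates is ordinary data management that a full protocol, the training manual or the SAP may contain, and silence does not prove that no check exists. That stands as a caution: the point concerns what the described procedure does if followed as written. It does not remove the point, because the eligibility rules and data flow are itemised in detail, the overlap problem was considered for shared records, and nothing shown leads to a check between separate practices.

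A reader might infer that double entry is undetectable and beyond repair. The documents do not support this. The remaining dates and age can flag probable duplicates, and Dataset 5 stays on the register's server, whose staff received every list with name, Medicare number and date of birth. What is true is narrower: analysts holding only the de-identified file cannot confirm duplicates, least of all among people who never returned a kit.

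A reader might also infer heavy contamination from snowball recruitment and the 40% of practices in rural or smaller regional places. Nothing in the document shows that trial practices are neighbours, and the Queensland figures point to about 1% or less unless they cluster locally.

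Nor does every duplicate pull the estimate towards zero. The roughly 32% in the same arm dilute nothing. Counting one outcome in two arms and ignoring the correlation is a variance matter, and it is conservative for that contrast.

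**Conclusion.** The gap stands. A person can be eligible at more than one trial practice, no comparison of lists is described, and given overlap the two records fall in different arms about 68% of the time.

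The consequence is modest. On the planned rates, and assuming that a doubly listed person responds at the higher applicable rate, a 10-point contrast becomes about 9.9 points at 1% overlap and still about 9.3 at 10%. The 1% and 10% figures are assumptions, the latter probably too high. The bias is towards the null, so it would not create a false finding of benefit. The sample size is not put in doubt: with all 21 practices per arm retained, power for the hardest contrast stays above 80% throughout this range. This is a cheap improvement to make, not a threat to the trial's conclusions.

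**What to change.** At Step 4, once all lists are in and before randomisation, have the NCSR compare Medicare number and date of birth across all 63 lists. Each person found on more than one list is either kept under one practice by a rule fixed in advance, and dropped from the other list and its weekly SMS files, or removed from all lists and all weekly SMS files. Report the count, even if it is zero. Add one sentence to the patient eligibility criteria stating that a person can be eligible at one trial practice only.

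The cost is one extra check by the NCSR staff member whom the trial already funds; it cannot be run until the last list has arrived. If duplicates are removed, a few people who attend several practices are lost. That slightly narrows the population, but because it happens before allocation it cannot depend on arm.
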